### Interventions

#### Graded exercise therapy

Participants assigned to the GET group will receive a 12-week supervised exercise programme in addition to UC. The treatment protocol *‘GET for fatigue in incurable cancer patients’* was developed by the study investigators in cooperation with a physiologist (MH) and physical therapist (MN) experienced in exercise programmes for cancer patients. The treatment protocol was based on the protocol for a previous pilot-study in patients with incurable cancer [20]. Physical therapists affiliated with the participating hospitals or from local physical therapy centres will deliver the GET. All therapists will be instructed about the treatment protocol and use of registration forms before enrolment of participants. Throughout the study, supervision will be provided upon request by a physical therapist (MN).

GET will be given by physical therapists individually or in small groups with a maximum of 5 participants, depending on the accrual rate. During the intake session, the physical therapist will collect information about a participant’s physical fitness level (by means of a submaximal test) and physical limitations. Participants will formulate treatment goals in activities of daily living together with the physical therapist, such as performing activities or leisure interests in the foreseeable future that are currently difficult to perform because of a lack of muscle strength or cardiopulmonary fitness. After the intake session, participants will receive weekly two-hour sessions of individually graded training supported by a physical therapist and adjusted to their abilities. In order to adjust the training to an individual participant, their heart rate reserve (HRR) and muscle strength (by means of one-repetition maximum [1RM] tests) will be determined during first session and after every three sessions. The two-hour GET sessions will include a warming up (10 min), high intensity aerobic interval training (35 min), a break (15 min), resistance training (35 min), and a cooling down (10 min). Additionally, there are 15 min available for evaluation of the GET session. In addition to this supervised session, participants are offered to practise in a second weekly session. After every three sessions, training progress will be evaluated and the programme will be adjusted by means of the newly determined HRR and 1RM and discussion of formulated treatment goals.

##### Aerobic training

The aerobic training will consist of cycling on an interval basis prior to the resistance training. Intervals will include alternated bicycling for four minutes at 60% (increasing to 80%) of participants’ HRR with three minutes on 35% (increasing to 50%) of HRR. Heart rate will be monitored during the aerobic training using a Polar® breast band (Polar T31 Breast Band, 2008, Polar Electro, Finland). We will use the Borg Scale of Perceived Exertion after each cycling interval to gauge the perceived intensity of the aerobic training [34].

##### Resistance training

The resistance program will include a circuit of seven exercises targeting large muscle groups important for activities of daily living. The following exercises will be executed: (1) leg press; (2) lunge; (3) vertical row; (4) lateral pull down; (5) abdominal crunch; (6) pull over; and (7) bench press. Exercises will be executed at 60-80% of participants’ 1RM and will consist of 3 sets of 8 to 12 repetitions. Some exercises will be performed more often based on the participants’ difficulties in this area and his or her goals in activities of daily living. Progression will be conducted by the graded activity principle, which states that the focus is on successes and positive experiences and that negative experiences will be prevented as much as possible [35].

#### Cognitive behaviour therapy

Participants in the CBT group will receive *‘CBT for fatigue in incurable cancer patients’* in addition to UC. This intervention was developed by the study investigators based on the evidence-based protocol of CBT for post-cancer fatigue [23, 26]. Adaptations were done for application with our new target population. This adapted CBT will consist of a maximum of ten sessions over a period of 12 weeks (i.e., one assessment session and maximum nine individual one-hour face-to-face treatment sessions). Qualified and trained psychologists will deliver CBT for fatigue. Prior to intervention delivery, all therapists will receive a three-day training provided by two experienced clinical psychologists (HK and TB). This training will provide background and rationale for each of the intervention modules and involves role-playing to practise the intervention components. An experienced clinical psychologist (HK) will provide on-going supervision to CBT therapists throughout the study.

CBT for fatigue in incurable cancer patients includes several modules aimed at fatigue-perpetuating cognitions and behaviours. Participants randomised to CBT will complete a set of additional questionnaires prior to the first intervention session to assess potential perpetuating factors (see Table 2). During the first intervention session it will be determined by the therapist which factors are applicable for the particular patient, which leads to a tailored-made intervention as only the relevant treatment modules will be selected. The goal of CBT is reduction of severe fatigue and fatigue-related disability. All participants will start with setting their treatment goals. Participants will be helped to formulate concrete goals in behavioural terms, such as resuming activities or leisure interests in the foreseeable future that are discontinued because of being severely fatigued. Then, therapists and participants will work on adjusting the fatigue-perpetuating factors that are applicable to the individual participant: (1) sleep problems and deregulated sleep-wake cycle; (2) dysfunctional cognitions regarding cancer (prognosis) and cancer treatment; (3) dysfunctional fatigue-related cognitions; (4) deregulated activity pattern; (5) negative social interactions and low perceived social support. Each of these perpetuating factors corresponds to a treatment module:

**Table 2 Tab2:** Instruments to assess which CBT modules are indicated

CBT Module	Instrument	Rating (RANGE)	Cut-off value
Sleep problems and deregulated sleep-wake cycle	Sleep-wake diary	Bedtimes and wake up times of 12 consecutive days and nights	Visual inspection of bedtimes and wake up times
	Sickness Impact Profile [41]: subscale Sleep and Rest	Number and type of items endorsed, weighted according to a standardised weighting scheme	Score ≥ 60
	Symptom Checklist-90 [52]: subscale Sleeping Problems	5-point Likert scale (3–15)	Score ≥ 6
Dysfunctional cognitions regarding cancer (prognosis) and cancer treatment	Impact of Event Scale [53]: subscale Intrusion subscale Avoidance	4-point Likert scale (7–28) 4-point Likert scale (8–32)	Score ≥ 10 Score ≥ 10
	Pictorial Representation of Illness and Self Measure [54]	Self-illness separation (SIS) in cm Self-fatigue separation (SFS) in cm	Fatigue-related suffering: SIS > SFS Illness-related suffering: SFS > SIS
	Illness Cognition Questionnaire [55, 56]: subscale Acceptance subscale Helplessness	4-point Likert scale (6–24) 4-point Likert scale (6–24)	Score ≤ 12 Score > 14
	Beck Depression Inventory-II Primary Care [57]	4-point Likert scale (0–21)	Score ≥ 4
	Hospital Anxiety and Depression Scale [58]: subscale Anxiety subscale Depression	4-point Likert scale (0–21) 4-point Likert scale (0–21)	Score ≥ 9 Score ≥ 9
Dysfunctional fatigue-related cognitions	Fatigue Catastrophising Scale [45]	5-point Likert scale (10–50)	Score ≥ 16
	Self-Efficacy Scale [26, 59]	4-point Likert scale (7–28)	Score ≤ 19
	Illness Management Questionnaire-factor III [60]	6-point Likert scale (9–54)	Score ≥ 30
	Anxiety for Fatigue	4-point Likert scale (8–32)	Score ≥ 14
Deregulated activity pattern	Actigraphy during 12 consecutive days	Number of days with a mean physical activity level > 66	Low-active: 0-1 Relatively-active: ≥ 2
	Sickness Impact Profile [41]: subscale Social Interactions	Number and type of items endorsed, weighted according to a standardised weighting scheme	Score ≥ 100
	Checklist Individual Strength [33]: subscale Concentration	7-point Likert scale (5–35)	Score ≥ 18
Negative social interactions and low perceived social support	Van Sonderen Social Support Inventory [61] (shortened version): subscale Negative Interactions subscale Discrepancies	4-point Likert scale (7–28) 4-point Likert scale (8–32)	Score ≥ 10 Score ≥ 14

##### Module 1: Regulation of sleep-wake cycle and improving sleep hygiene

The patient will be explained how the ‘biological clock’ can be reset, in order to establish a consistent sleep-wake pattern with regular bed and wake-up times and no day-time napping. If necessary, advice with respect to sleep hygiene will be given.

##### Module 2: Reformulate dysfunctional cognitions regarding cancer and cancer treatment

This module aims to help the patient formulate more helpful beliefs to improve his or her coping with the fact of having incurable cancer, including fear of the future, and experiencing side effects of cancer treatment. Dysfunctional beliefs will be discussed and restructured.

##### Module 3: Reformulate dysfunctional cognitions regarding fatigue

The goal is to increase self-efficacy with respect to fatigue, reduce fatigue catastrophising, and help the patient to focus less on fatigue.

##### Module 4: Regulation of activity

Two activity patterns will be distinguished on the basis of actigraphy (see *‘Outcomes’*): relatively active or low active. Some severely fatigued patients have a persistent low level of physical activity, while others have a more fluctuating activity pattern with bursts of activities followed by periods of inactivity (‘all-or-nothing behaviour’). Both activity patterns can perpetuate fatigue. Relatively active participants are helped to spread their physical, mental, and social activities more evenly over the day and week. Subsequently, participants will gradually increase their physical activity level by means of a daily walking or cycling program of their choice. The chosen activity will be gradually and systematically increased. Low active participants will be motivated to immediately start with the graded activity program. By increasing physical activity, participants’ self-efficacy with respect to physical activity and fatigue will often change positively. Eventually, participants will also increase mental and social activities.

##### Module 5: Improve social support and change unhelpful social expectations

This module is directed at modifying the patients’ unhelpful cognitions regarding their social environment, as they can maintain fatigue. Unrealistic expectations towards others are detected and disputed. Patients will practise with exercises in order to change these unhelpful cognitions and are encouraged to involve their partner in this module. Also, coping strategies in contact with others, such as family, friends, and/or colleagues, will be discussed.

After addressing the perpetuating factors of fatigue, patients will gradually work towards realising the treatment goals formulated at the start of the intervention. At the end of the intervention it is discussed how to deal with new episodes of fatigue, that may be induced when starting further lines of systemic cancer treatment.

#### Usual care and use of co-intervention

All participants will be treated for incurable cancer in concordance with national and regional cancer clinical practice guidelines of the Dutch Comprehensive Cancer Centres [36]. Participants assigned to the control group have no access to one of the two study interventions, but may be referred by their oncologist or general practitioner to physical therapists or psychologists as part of UC. Participants assigned to CBT will be asked not to follow an exercise programme as part of UC simultaneously, and participants assigned to GET will be asked not to follow a psychological intervention as part of UC simultaneously. We will collect information on whether participants have engaged in exercise programmes or psychological interventions as part of UC at all three post-randomisation assessments (T1, T2, and T3).

### Adverse events

All adverse events (AEs) and serious adverse events (SAEs) reported spontaneously by the participants or observed by the GET or CBT therapists will be recorded. All reported AEs will be followed until they have aborted, or until a stable situation has been reached. SAEs are defined as any medical occurrence that results in death, is life threatening, requires hospitalisation, results in persistent or significant disability or incapacity, or a new event of the study likely to affect the safety of participants. SAEs will be reported to the Research Ethics Committee of the University-affiliated hospital that approved the study protocol. At post-intervention assessment (T1), patients will be asked whether they think they currently experience or have experienced AEs as a result of the intervention (GET or CBT) they have received. In case of an affirmative answer, patients will be asked to specify these AEs.

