### Procedure

Eligible patients willing to participate in the study will be asked to sign informed consent upon which they will be invited by a research assistant to complete the baseline assessment (T0) at their own hospital. Upon completion of T0, the research assistant will use a central web-based randomisation service to randomly allocate a participant to one of the three study arms: (1) GET in addition to UC; (2) CBT in addition to UC; or (3) control group receiving UC (see Fig. 1). Participants assigned to GET or CBT will start the intervention approximately two weeks after T0. Both interventions will be delivered at or near their own hospital over a period of 12 weeks. Participants assigned to CBT will complete a set of additional questionnaires to determine relevant intervention modules prior to the first intervention session. Participants assigned to GET will complete an additional submaximal test to determine physical fitness during the first intervention session. At 14 weeks, participants are invited by the research assistant to complete the post-intervention assessment (T1) at the hospital. Follow-up assessments at 18 weeks (T2) and 26 weeks (T3) are entirely web-based and will be completed at home. For participants that do not have Internet access, a paper version of the follow-up questionnaires will be send to their home address, which can be returned in a self-addressed, pre-stamped envelope.

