### Outcomes

Outcome measures and data collection time points are listed in Table 3. The primary endpoint of this study is the post-intervention assessment (T1), 14 weeks after randomisation. Primary and secondary outcomes will be measured at baseline (T0), post-intervention (T1) and follow-up (T2, T3). Proposed mediators will only be assessed at T0 and T1.

**Table 3 Tab3:** Data collection time point of all outcome measures and proposed mediators

Concept	Questionnaire	Measurement time points			
		T0	T1	T2	T3
Socio-demographics	Self-report questionnaire	X			
Medical characteristics	Medical chart review	X	X		
Primary outcome:					
Fatigue severity	CIS *fatigue severity*	X	X	X	X
Secondary outcomes:					
Fatigue	EORTC QLQ-C30 *fatigue*	X	X	X	X
Quality of life	EORTC QLQ-C30 *global health status*	X	X	X	X
Functional impairments	SIP	X	X	X	X
	EORTC QLQ-C30 *emotional functioning*	X	X	X	X
	EORTC QLQ-C30 *physical functioning*	X	X	X	X
Proposed mediators:					
Physical activity	Actigraphy during 12 consecutive days	X	X		
Physical fitness	6MWT	X	X		
Self-efficacy	SES	X	X		
Fatigue catastrophising	FCS	X	X		

*T0* baseline (pre-intervention), *T1* post-intervention/UC (14 weeks post-randomisation), *T2* first follow-up assessment (18-weeks post-randomisation), *T3* s follow-up assessment (26-weeks post-randomisation)

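### Adverse events are ascertained unequally: usual care relies on spontaneous reports, while GET and CBT add therapist observation and a solicited T1 question, so event rates cannot be fairly compared with usual care

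*Protocol article*

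**What the plan says.** The Adverse events section applies one recording rule to adverse events and serious adverse events alike: those "reported spontaneously by the participants or observed by the GET or CBT therapists will be recorded". It adds one solicited item, at T1 only, in which patients are "asked whether they think they currently experience or have experienced AEs as a result of the intervention (GET or CBT) they have received".

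The section on usual care states: "Participants assigned to the control group have no access to one of the two study interventions". Usual-care participants may be referred to a physical therapist or psychologist in ordinary practice, but those professionals are not named as observers of events.

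Planned contact differs by arm. In GET, "participants will receive weekly two-hour sessions of individually graded training supported by a physical therapist". For CBT: "This adapted CBT will consist of a maximum of ten sessions over a period of 12 weeks". The contact common to all arms is the visit described under Procedure: "At 14 weeks, participants are invited by the research assistant to complete the post-intervention assessment (T1) at the hospital". Table 3 (Outcomes) also lists "Medical chart review" at T0 and T1 for medical characteristics, without restriction by arm, but the article does not name it as a source of adverse events.

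**The concern.** Two of the three routes exist only where there is a study intervention. Patients with advanced cancer on systemic treatment will have many events unrelated to GET or CBT. A therapist who sees a participant about weekly will learn of some events that a usual-care participant, for whom the article describes no study contact between baseline and 14 weeks, would never volunteer. Set side by side, the counts would then mix true harm with opportunity to be recorded, and the bias would run towards more events in the intervention arms.

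This matters because the Discussion says that one or both interventions might become part of usual care if efficacious. That decision weighs benefit against harm relative to usual care, and a real excess with exercise could not be told apart from closer observation.

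**Working it through.** The plan states no figure on this point, so the first check sets the routes against the arms.

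| Route (Adverse events section) | GET | CBT | Usual care |
|---|---|---|---|
| Spontaneous report by the participant | yes | yes | yes |
| Observation by study therapist | yes, weekly sessions | yes, up to ten sessions in 12 weeks | no |
| T1 question on events attributed to GET or CBT | yes, if T1 is attended | yes, if T1 is attended | not answerable as worded |

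Usual care has one route and each intervention arm has three. GET and CBT share the same routes, though with different contact time.

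The T1 question also reaches only those who attend T1. The sample size section expects 30% attrition from 73 per arm: 73 × 0.30 = 21.9, so about 22 participants per arm would not be asked.

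The second check asks how far unequal detection could move a comparison. The inputs are:

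- n = 73 per arm (sample size section).
- True event risk p, equal in both arms. This is assumed: 30%, with a range of 20% to 50%.
- Detection d₁ = 90% in an intervention arm and d₀ = 90%, 70%, 50% or 30% in usual care. These are assumed, because the article gives no detection figures.

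The formulas are:

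- Expected recorded count = n × p × d.
- Apparent risk ratio = (p·d₁)/(p·d₀) = d₁/d₀, which does not depend on p.
- Chance of a nominally significant false excess in the intervention arm, at two-sided 0.05, = Φ[(Δ − 1.96·SE₀)/SE₁]. Here Δ = p(d₁ − d₀), SE₀ is the pooled standard error and SE₁ the unpooled one.

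Results for p = 30%:

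| Detection in usual care | Expected counts, intervention vs usual care | Apparent risk ratio | Chance of false significant excess |
|---|---|---|---|
| 90% | 19.7 vs 19.7 | 1.00 | 2.5% |
| 70% | 19.7 vs 15.3 | 1.29 | 13% |
| 50% | 19.7 vs 11.0 | 1.80 | 43% |
| 30% | 19.7 vs 6.6 | 3.00 | 82% |

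For example, at 50%: Δ = 0.27 − 0.15 = 0.12; SE₀ = √(2 × 0.21 × 0.79/73) = 0.0674; SE₁ = √((0.27 × 0.73 + 0.15 × 0.85)/73) = 0.0667. This gives (0.12 − 0.1321)/0.0667 = −0.18 and Φ = 0.43.

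Over true risks of 20% to 50%, the chance of a false excess is 10% to 23% at 70% detection and 28% to 72% at 50% detection. The ratio only returns the detection rates that were put in. The table shows direction and sensitivity and does not estimate the bias in this trial.

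**The case against.** The case on the other side has real substance.

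- **Usual care is not uncovered.** Spontaneous reports are recorded whatever the arm, and neither the definition of serious events nor their reporting to the ethics committee is restricted by arm. This stands: capture in usual care is less complete, not absent.
- **Objective events depend little on a therapist.** Deaths, and to a lesser degree hospitalisations, may be found almost equally in all arms. The article also records why participants leave the intervention or miss assessments, and the causes of missing data. This stands in part. Those records would bring many deaths to light, but as reasons for dropout, and the rule for recording serious events still names only the two routes.
- **The T1 question leaves out background events by design.** It asks only about events the patient attributes to GET or CBT, so it does not itself inflate the count of cancer-related events. This stands. Inflation of background events would come through therapist observation. The question adds a count that has no usual-care counterpart.
- **No comparison of harms with usual care is promised.** The aims and the statistical analyses contain none. This stands, and it limits the point to any by-arm table or safety statement that may later be made.
- **A journal article condenses the full protocol.** Forms and elicitation procedures may be fuller there. That would answer a complaint about missing detail, but here the article states the routes, and as stated they are unequal.

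A reader might infer that no valid comparison of harms is possible, or that the trial could support no safety statement at all. The documents do not support either inference. Objective serious events could be compared if captured alike in every arm, GET and CBT share the same routes, and harm that patients attribute to an intervention can be described within each of those two arms.

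**Conclusion.** The asymmetry is real and follows directly from the stated collection rules. As described, adverse event rates in GET or CBT, especially of non-serious events, cannot be fairly compared with usual care, and the expected direction of bias is towards more recorded events in the intervention arms. Its size cannot be known from the article. The illustrated ratios of 1.29 to 3.00 rest wholly on assumed detection rates and shrink to 1.00 if detection is equal, as it may nearly be for deaths. The efficacy analyses are unaffected.

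**What to change.** 1. At the existing T1 assessment, ask all three arms the same question about adverse events, with no reference to an intervention or to cause. The same item could optionally be added to the T2 and T3 questionnaires.
2. Extract deaths and hospitalisations for every randomised participant, including those who miss T1, from the chart review already planned at T1.
3. Use only these common sources for any by-arm harms table.
4. Keep therapist-observed events and the existing attribution question, and report them separately as descriptive data for GET and CBT.

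The cost is a few questionnaire items, one chart-review field and a small amendment, with slight extra burden for respondents and abstractors. Recruitment was already under way when the article was written, so participants enrolled before the amendment may be covered by chart review only. The report should say how many there are in each arm.
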